### Trial outcomes and measures

During the feasibility and full-scale portions of the trial, we will assess participants’ experience with the program and will collect outcomes that will be used to evaluate intervention effects in the full-scale portion of the trial. Participant satisfaction with the intervention will be assessed 3 months post-randomization among intervention participants using an adapted version of the 8-item Client Satisfaction Questionnaire (CSQ-8) [47]. During the feasibility portion of the trial, participants will also be asked open-ended questions about their experience in the program, including challenges, positive elements, and suggestions for improvement, using an adapted version of the Patient Education Assessment Tool (PEMAT) [48]. Logins to the online program and usage of program components will also be assessed using automated usage logs collected through the online SPIN-SELF platform. Feasibility elements of trial procedures and the delivery of the SPIN-SELF Program will be tracked by the research team throughout the feasibility trial. See Table 1 for a detailed description of feasibility outcomes.

The primary outcome analysis in the full-scale trial will compare SEMCD Scale scores [38] between participants randomly assigned to the SPIN-SELF Program versus care as usual control at 3 months post-randomization. Secondary outcomes will include SEMCD scores 6 months post-randomization, patient activation scores at 3 and 6 months post-randomization using the Patient Activation Measure (PAM-13) [49], social appearance anxiety scores at 3 and 6 months post-randomization using the Social Appearance Anxiety Scale (SAAS) [50], and functional health outcomes at 3 and 6 months post-randomization using the Patient Reported Outcomes Measurement Information System profile version 2.0 (PROMIS-29v2) [51].

#### CSQ-8 [47]

The 8-item CSQ-8, which measures client satisfaction with health care services, has been adapted to assess participant satisfaction with the SPIN-SELF Program. Items are scored on a 4-point scale from 1 (low satisfaction) to 4 (high satisfaction). Total scores range from 8 to 32, with higher scores indicating higher satisfaction. The CSQ-8 is available in English and French [52].

#### PEMAT [48]

The adapted PEMAT is a 23-item questionnaire that allows participants to provide comments on their experiences with the format and procedures of the trial, the program content, group sessions, and other input. Responses are assessed qualitatively. The PEMAT is available in English and French.

#### Program usage

Usage among participants in the intervention group will be examined via automated intervention usage log data. These data will provide information on online program logins and usage of specific modules.

#### SEMCD [38]

The SEMCD is a 6-item measure that evaluates confidence in ability to manage fatigue, pain, emotional distress, and other symptoms; to do things other than take medications to reduce illness impact; and to carry out tasks and activities that may reduce the need to see a doctor. Items are rated on a 1 (not confident at all) to 10 (totally confident) scale. The total score is the mean of all items, and ranges from 1 to 10. SEMCD scores have been validated in SSc through the SPIN Cohort in English and French [53].

#### PAM-13 [49]

Patient activation, which reflects the extent to which patients effectively engage with and manage their own health [49, 54], will be assessed with the 13-item PAM-13. The PAM-13 includes 13 statements related to participants’ attitudes and perspectives about their health, with four possible responses ranging from (1) strongly disagree to (4) strongly agree, with an additional “Not applicable” option. Using calibration tables, participants’ responses are converted into raw scores ranging from 0 to 100, with higher scores indicating higher activation [55]. PAM-13 scores have demonstrated reliability and validity in many chronic conditions [56–58]. The PAM-13 is available in English and French [55].

#### SAAS [50]

The SAAS consists of 16 items that measure patients’ self-reported anxiety related to situations where one’s appearance will be evaluated, with response options ranging from 1 (“Not at all”) to 5 (“Extremely”). To calculate total scores, the first item (“I feel comfortable with the way I appear to others”) is reverse-coded, all items are summed, and total scores range from 16 to 80, with higher scores indicating greater anxiety. SAAS scores have been validated as a measure of social appearance anxiety for people with SSc through the SPIN Cohort in English and French [59, 60].

#### PROMIS-29v2 [51]

The PROMIS-29v2 measures 8 domains of health status with 4 items for each of 7 domains (physical function, anxiety, depression, fatigue, sleep disturbance, social roles and activities, pain interference) plus a single item for pain intensity. Domain items are scored on a 5-point scale (range 1–5), with different response options for different domains. The single pain intensity item is measured on an 11-point rating scale. Higher scores represent more of the domain being measured; that is, better physical function and ability to participate in social roles and activities, but higher levels of anxiety, depression, fatigue, sleep disturbance, pain interference, and pain intensity. Total raw scores are obtained by summing item scores for each domain, which are converted into T-scores standardized in the general US population (mean = 50, standard deviation = 10). The PROMIS-29v2 scores have been validated in SSc in English and French [61, 62].

### Sample size

A Cochrane Review (*N* = 7,442) of lay-led self-management programs reported a standardized mean difference (SMD) effect size of 0.3 (95% confidence interval [CI] 0.19 to 0.41) for improved self-efficacy in 10 studies [63]. With a 1:1 randomization ratio, for an assumed effect size of SMD = 0.30, two-tailed *α* = 0.05, a mean of 8 participants per group, and intra-class correlation coefficient of 0.08 (based on SPIN-CHAT results) [27], *N* = 471 provides ≥ 80% power. In our recent SPIN-CHAT [27] and SPIN-SSLED trials [35, 36], which used similar group formats, loss to follow-up was well below 10%. Assuming 10% loss to follow-up would require 524 participants. In the 3 months between March 1, 2021 and June 1, 2021, 1007 SPIN Cohort participants completed assessments, of whom 986 completed the SEMCD Scale; of these, 524 (53%) met SPIN-SELF eligibility criteria. Over 50% of SPIN-CHAT [27] participants were recruited externally, and we expect similar external recruitment for SPIN-SELF to supplement SPIN Cohort participants, which will allow us to meet our recruitment target.

### Recruitment

Eligible SPIN Cohort participants identified via routine cohort assessments will receive an email from a SPIN Team member sent using an automated email feature in the *Qualtrics* platform to introduce the SPIN-SELF Program and explain the enrollment procedure and what participation involves. The email will contain a secure *Qualtrics* survey link by which participants will have the opportunity to consent, decline, or request to be contacted by a study team member for more information. Those who consent will also provide days and times when they could take part in group sessions.

Additionally, recruitment announcements will be posted on SPIN’s Facebook page and Twitter account and distributed via SPIN’s patient organization partners in countries with large English-speaking populations (feasibility and full-scale trials; Canada, USA, UK, Australia, New Zealand, Philippines) and French-speaking populations (full-scale trial; Canada, France). Recruitment announcements for non-SPIN Cohort participants will direct potential participants to a different *Qualtrics* survey link with information on the trial and a consent form for the completion of eligibility questionnaires online, items to assess eligibility, similar consent options for trial participation as SPIN Cohort enrollees for those who are eligible, and days and times available for those who are eligible.

Consent forms for the feasibility portion of the trial will explain (1) that the purpose of the feasibility trial is to test the procedures and intervention delivery prior to proceeding to the full-scale trial; (2) that if based on the feasibility trial we determine that no substantive changes are needed to procedures we will proceed directly to the full-scale trial with data from the feasibility study included in the full-scale RCT; and (3) that if substantive changes are required, the feasibility trial data will be analyzed separately from the full-scale trial.

Consent forms for both the feasibility and full-scale portions will explain that (1) new intervention groups will be started on an approximately monthly basis; (2) each month, enrolled participants with availabilities compatible with scheduled groups will be randomly selected and assigned to an intervention group or care as usual control with 1:1 allocation ratio; (3) participants randomized to the SPIN-SELF intervention group, plus those allocated to care as usual, will complete outcome measures online at 3 and 6 months post-randomization through *Qualtrics*; (5) depending on availabilities, it is possible that some enrolled participants will not be able to be randomized; and (6) enrolled participants who do not receive the intervention as part of the trial, either because they are selected for the control group or because they are not randomly assigned to either the intervention group or control, will be offered access to the online-only SPIN-SELF Program version after the full-scale trial but will not be placed into videoconference groups. A member of the SPIN research team will call all consented participants to confirm availability, time zone, and answer any questions they might have prior to including them in the pool of participants eligible for randomization. Potential participants who decline enrolment in the SPIN-SELF trial will not be reassessed for eligibility if they are again eligible at a future SPIN Cohort assessment.

Recruitment will be paused once our enrollment target for the feasibility trial has been reached. We will restart at the beginning of the full-scale trial.

### Random selection and allocation

For the feasibility and full-scale portions of the trial, consented participants will be entered into pools of participants available to participate in the same weekly group based on availability and, for the full-scale trial, language. For the full-scale trial, separate English- and French-language groups will be formed (feasibility only includes English-speaking participants). De-identified codes for participants in each pool will be provided to an external randomization service. Starting with the largest pool, the service will randomly select the largest possible even number of participants (12 to 20 participants to obtain intervention groups of 6 to10 participants) then randomly allocate half to intervention and half to control via single block randomization using R version 3.6.3. For the feasibility trial, depending on scheduling availability and pool sizes, we will form 2–3 pools. For the full-scale trial, we will form as many pools as possible each month until the enrollment target is met.

All participants who are randomized will receive an email to communicate their assignment to the SPIN-SELF Program or usual care. The intervention group email will include the date and time of their first group session and information on how to access SPIN-SELF Program and login to the videoconferencing system. Participants who have not been randomly assigned to either the intervention group or the waitlist will receive an email to inform them that they could not be assigned but will be re-contacted to confirm eligibility and interest and attempted to be randomized when new sessions begin again in a month.

### Blinding and protecting against sources of bias

In most pragmatic trials of education and psychological interventions, including the SPIN-SELF Trial, participants are typically not able to be blinded to intervention status. This may be understood as part of the response to being offered an intervention, as may occur in clinical practice [64]. Another concern relates to the potential for contamination if participants randomized to the control group can also access the program. This risk of this, however, is minimal. Program materials are accessible only via the secure intervention website, and we will request that intervention participants do not share their access information with others. Study staff who interact with participants to provide help with access or other issues will not be blind to intervention status. Outcome assessment will not be blind, since it is self-report and will be done by participants not blind to their status. Statistical analyses cannot be blinded due to the PN-RCT design in which participants in the intervention arm, but not control, are nested.

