### Data analysis

Consistent with the feasibility trial design and small sample size, no hypothesis tests are planned for the feasibility portion of the trial [66, 67]. Instead, we will present a description of the feasibility elements, including participants’ eligibility and recruitment and numbers and percentages of participants who respond to follow-up measures. Use of the internet intervention will be described by presenting the frequency of logins and usage of the specific SPIN-SELF modules. Analysis of outcome measures will include the completeness of data and presence of floor or ceiling effects. Descriptive statistics will be used to provide means and standard deviations for the measures. Qualitative information on participants’ experience using the SPIN-SELF intervention will be used to interpret acceptability related to the group-sessions format, content of the sessions and online program, webpage organization, and navigation. Information related to required resources and management of the program during feasibility will inform any necessary changes to intervention or trial procedures.

In the full-scale trial, we will use intent-to-treat analyses to estimate score differences between intervention and care as usual participants with a linear mixed-effects model fit using the lmer function in lme4 [68]. Score differences and Hedges’ g SMD effect size will be presented with 95% CIs. For all models, to account for clustering in the blocked PN-RCT design, we will fit a random intercept and slope for treatment effect by randomization block and an additional random slope for treatment by intervention group cluster [30, 69]. In main analyses for each outcome, in addition to a fixed effect for assignment to the intervention arm, we will include a fixed effect for baseline score. In adjusted analyses, we will also control for age (years), sex (male vs. female), SSc disease subtype (diffuse vs. limited), disease duration (years since diagnosis), and country (e.g., Canada, France, other vs. USA) as fixed effects.

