To minimize the possibility of bias from missing outcome data, we will use multiple imputation by chained equations using the mice [70] package to generate 20 imputed datasets, using 15 cycles per imputed dataset. Variables in the mice procedure will include randomization block, intervention arm, number of videoconference sessions attended, measures of all primary and secondary outcomes at baseline and at 3 and 6 months post-randomization, age, sex, SSc disease subtype, years since diagnosis, country (e.g., Canada, France, UK, Australia, other vs. USA), and race/ethnicity (e.g., Black and other vs. White). Pooled standard errors and associated 95% CIs will be estimated using Rubin’s rules [71].

To estimate average intervention effects among compliers (to be defined pre-analysis based on session attendance or online program usage), we will use an instrumental variable approach to inflate intent-to-treat effects from main models by the inverse probability of compliance among intervention arm participants [72, 73]; 95% CIs will be constructed via a cluster bootstrap approach, resampling at study randomization block and participant levels [74, 75]. For transparency, results for participants with complete data will also be shown.

Participant satisfaction scores for the intervention group will be reported descriptively.

All outcome analyses will be conducted in R (R version 3.6.3; R Studio version 1.2.5042). All analyses will be 2-sided with *α* = 0.05. We will not adjust for multiple analyses since we identified a single primary outcome a priori.

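### Partial nesting does not by itself prevent blinded analysis: the main model can be coded and fitted on masked arm labels, and what reveals the arm is attendance and usage data

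*Protocol article*

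**What the plan says.** Under Blinding and protecting against sources of bias, the protocol article states that "Statistical analyses cannot be blinded due to the PN-RCT design in which participants in the intervention arm, but not control, are nested". It gives no other reason. The same section says "Outcome assessment will not be blind, since it is self-report and will be done by participants not blind to their status" and "Study staff who interact with participants to provide help with access or other issues will not be blind to intervention status", and it explains that participants cannot be blinded either.

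Under Random selection and allocation, an external service selects an even number of people from each availability pool ("12 to 20 participants to obtain intervention groups of 6 to10 participants) then randomly allocate half to intervention and half to control").

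Under Data analysis, all models are to have a "random intercept and slope for treatment effect by randomization block and an additional random slope for treatment by intervention group cluster", fitted with lmer. The imputation variables include "randomization block, intervention arm, number of videoconference sessions attended". The complier analysis rests on a definition still "to be defined pre-analysis based on session attendance or online program usage".

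**The concern.** The protocol treats masking of the analysis as impossible and puts this down to the one-sided grouping. If that reason is mistaken, the trial gives up the one stage at which masking is feasible. Participants, participant-facing staff and the self-reported primary outcome are all described as unblinded.

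Two decisions visible in the text could be influenced by seeing arm and outcome together.

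- **Complier definition.** It is not yet fixed. The complier estimate is the intention-to-treat effect divided by the proportion of compliers in the intervention arm, so the threshold directly scales the reported size.
- **Random effects of the primary model.** With one group per block, two of the planned random terms cannot be told apart, so some simplification is foreseeable. The choice can change the standard error of the primary estimate.

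**Working it through.** **1. The plan's own figures.** Inputs from Sample size: SMD 0.30, two-sided alpha 0.05, 80% power, mean group size 8, ICC 0.08, 1:1 allocation, 10% loss. Take residual SD 1 in both arms and add between-group variance ICC/(1 − ICC) = 0.08/0.92 in the intervention arm only:

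N = 2 × (z₀.₉₇₅ + z₀.₈₀)² × (1 + 1 + 8 × 0.08/0.92) / 0.30² = 470.2, rounded up to 471 (power 80.1%). Then 471/0.90 = 523.3, rounded up to 524.

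Both figures reproduce. Nothing below alters them.

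**2. Where the group comes from.** A block of 12 to 20 people is split in half, and the intervention half of 6 to 10 is the videoconference group. Hence group = block × intervention arm. The two halves are of equal size at randomization, so size does not show which half met as a group. A group identifier left in the file would reveal the arm, but it carries nothing that block and arm do not already carry, so it can be left out.

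**3. The planned model under a label swap.** For person i in block j, with T = 1 for intervention and baseline score x:

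y = β₀ + β₁T + β₂x + u₀ⱼ + u₁ⱼT + vⱼT + e

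Here u₀ⱼ and u₁ⱼ are the block intercept and slope, and vⱼ is the group slope. With one group per block, u₁ⱼ and vⱼ multiply the same indicator and only their sum sⱼ = u₁ⱼ + vⱼ is identified. Put T = 1 − T′:

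y = (β₀ + β₁) − β₁T′ + β₂x + (u₀ⱼ + sⱼ) − sⱼT′ + e

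If intercept and slope are allowed to correlate, the pair (u₀ⱼ + sⱼ, −sⱼ) again has an unrestricted 2 × 2 covariance matrix. It is the same model in other parameters: same likelihood, same standard error, effect with opposite sign.

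**4. Numerical check.** Two simulated trials used groups of 6 to 10, ICC 0.08 and SMD 0.30. Assumed values are 33 blocks (524/16 = 32.75), block SD 0.2 and baseline slope 0.5. REML fits:

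| Model | Trial | Labels | Deviance | Effect | SE |
|---|---|---|---|---|---|
| Planned | 1 | correct | 1620.2572 | +0.3149 | 0.0834 |
| Planned | 1 | swapped | 1620.2572 | −0.3149 | 0.0834 |
| Planned | 2 | correct | 1464.2375 | +0.2299 | 0.0959 |
| Planned | 2 | swapped | 1464.2375 | −0.2299 | 0.0959 |
| Block intercept + group slope only | 1 | correct | 1620.2698 | +0.3149 | 0.0834 |
| Block intercept + group slope only | 1 | swapped | 1620.2698 | −0.3149 | 0.0834 |
| Block intercept + group slope only | 2 | correct | 1464.3115 | +0.2295 | 0.0983 |
| Block intercept + group slope only | 2 | swapped | 1466.2718 | −0.2391 | 0.0869 |

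The planned structure is symmetric in both trials, as the algebra requires. The reduced structure, with independent intercept and slope, is not symmetric in general: in trial 2 the swap changes the deviance, the effect size and the standard error. Symmetry therefore needs the correlated block slope as well as the one-group-per-block layout. In trial 2 the choice of structure alone moves the correctly labelled standard error from 0.0959 to 0.0983.

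**5. What does reveal the arm.** Control participants attend no sessions and have no program access during the trial. The attendance count in the imputation model therefore shows the arm, as do the attendance or usage data behind the complier definition.

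**The case against.** The strongest reply is that the conclusion is right even if the reason is not. Multiple imputation is the planned handling of missing outcomes, and complete-data results are shown only in addition. Attendance is an imputation variable, so the arm is visible before any model is fitted to the imputed data. This stands for those steps: the imputation as specified and the complier estimate cannot be run masked. It does not support the stated reason, and it does not stop coding decisions and model code from being settled beforehand on a masked file.

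A second reply is that partially nested models are generally not symmetric under a label swap. That is correct, as the reduced model shows. It does not apply to the structure this plan specifies.

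A third reply is that labels permuted within block break up the real groups, so convergence and variance estimates on that file say little about the real fit. This also stands, and the fix allows for it.

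A reader might infer that many analysis choices lie open, including country coding, data cleaning and non-convergence. The documents do not support that. The two country lists serve different purposes, adjustment and imputation, and do not conflict. Cleaning and convergence rules are commonly left to a statistical analysis plan, which is not shown. The primary outcome and time point, the baseline covariate, the adjustment variables and the imputation settings are fixed. The complier definition is already promised before analysis; what is not said is that it will be set without sight of outcomes.

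**Conclusion.** The sentence is wrong as an explanation. In this design partial nesting does not prevent masking of the main model, and attendance and usage data are what limit it. A reader might go further and infer that the whole analysis could be blinded, or that the primary result will be biased. Neither follows: the imputation with attendance and the complier estimate need true allocation, and nothing in the documents shows that a decision would be made on sight of the results.

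The point is of low severity. No sample size, power figure or planned estimate changes, and the bias avoided cannot be quantified from the documents. The benefit is protection of two decisions: the complier definition and the simplification of random terms that cannot be separated.

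The conclusion assumes one intervention group per block throughout, as the allocation section describes, and a block intercept and slope that are allowed to correlate, which is the lmer default. The label symmetry is algebraic and does not depend on the simulation values.

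**What to change.** Replace the sentence in the blinding section with a statement that:

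- (a) covariate coding, the model code and the rule for simplifying the random effects will be finalized and locked on a file holding block identifier and masked or permuted arm labels, without attendance, usage or group identifiers;
- (b) the complier definition will be fixed from attendance and usage data held without outcomes;
- (c) the imputation that uses sessions attended, and the complier estimate, will be run with true allocation only after the lock.

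The random-effects rule should follow from the known design, in which the group slope and the block treatment slope cannot be separated when each block has one group. It should not be chosen from variance estimates on permuted data, because permutation breaks the real group clustering.

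The cost is a wording change and a little data management; the external service already performs the allocation. The drawback is that a code error found after the lock needs a documented change.
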